### Participants and recruitment

Couples from the case group will be recruited from the infertility clinics in KKH, while couples from the control group will be recruited from the antenatal clinics in KKH. The team will recruit potential participants through local advertising in the hospital. We will collaborate with obstetricians and gynaecologists at KKH to obtain participant referrals. Moreover, active screening of potential participants will be conducted in the clinics. Other than from the antenatal and infertility clinics, the team will also leverage the Healthy Early Life Moments in Singapore (HELMS) programme to recruit potential cases and controls. HELMS is a new programme established at KKH in April 2022 to provide a continuum care for women with obesity in the general population before, during, and after pregnancy.^43^

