#### Cases

Men aged 21–49 years.Men with a female partner aged 21–39 years.Couples who are not able to conceive for at least 12 months of regular, unprotected intercourse.Couples who are Singapore citizens or permanent residents.

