#### Controls

Men aged 21–49 years.Men with a female partner aged 21–39 years.Men with proven fertility indicated by female partners who are currently pregnant and with viable intrauterine pregnancy at gestational weeks of less than or equal to 16 at the time of the study.Couples with attempted time to conceive within 12 months to achieve this pregnancy.Couples who are Singapore citizens or permanent residents.

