### Data collection and management

During the study visit (the only single timepoint visit), trained research staff will collect data on the sociodemographics and medical history of participants through interviews and medical record collection forms. They will also gather self-reported data on behavioural, lifestyle and environmental factor exposures from the past month using standardised questionnaires. The selection of the recall timeframe is based on the period specified in the validated questionnaires (table 1). Additionally, the staff will conduct anthropometric and body fat composition measurements, and collect blood, urine and semen samples from participants at the clinics in KKH. All data will be saved in a REDCap database. Access to this database is secured with a password, and only approved study team members can access the stored information.

**Table 1 T1:** Data and biosamples collected from both case and control participants

Male partners	Parameters
Sociodemographic, clinical, behavioural, lifestyle and environmental factors	Age, country of origin, length of time in Singapore if born overseas, ethnicity, education, occupation, monthly income, medical history, medication, family history, reproductive health history, male sexual function,^60^ environmental exposure, cigarette smoking, sleep,^61^ stress,^62^ dietary supplement intake, dietary and alcohol intake,^63^ chrononutrition profile,^64^ physical activity,^65^ sedentary behaviour
Anthropometric and blood pressure measures	Body height, weight, body fat composition (InBody 970, USA), blood pressure
Biochemical tests (blood/urine samples)	HbA1c, lipid profile, cortisol, oxidative stress, inflammatory biomarkers, environmental pollutants (endocrine-disrupting chemicals), exosomes, microbial-derived metabolites
Semen analysis	Semen volume, sperm density, sperm motility, sperm morphology, sperm DNA fragmentation
Molecular analysis	mRNA expressions, sncRNA expression, DNA methylation

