We will include the identified male factors from aim 1, along with female factors which are known to be associated with successful pregnancy in a multivariable logistic regression. The male factors will focus on those easily accessible measurements. The female factors include age, BMI, smoking exposure, dietary habit, alcohol consumption and folic acid supplementation, which we have identified in our previous study.^52^ We will also include some important clinical data and other maternal factors such as the duration of active conception attempts, sexual health issues and probable depression in the logistic regression to further select the predictors. To ensure accuracy, we will use weighted logistic regression, adjusting the model based on the updated prevalence of successful pregnancies within a year in the population to correct for sampling biases. The best-fitting model will be determined using Akaike’s information criteria. Subsequently, we will create a point-based scoring system based on the final model coefficients,^53^ making it easily applicable in community settings. Integer points will be assigned depending on the presence or absence of each factor, allowing the estimation of overall probability by summing the points. Higher point values will indicate higher chances of pregnancy. To facilitate calculation of the fertility index score, all continuous variables will be categorised based on clinical thresholds or appropriate percentiles prior to the analysis. We will repeat the same procedures by including male metabolic biomarkers and semen parameters that are associated with successful pregnancy in the weighted logistic regression. This will enable the generation of various versions of the fertility index, catering to different levels of complexity for application in primary and tertiary care settings.

Subsequently, we will use 10-fold cross-validation to assess the performance of the derived logistic regression models and respective fertility index scores. This cross-validation procedure helps evaluate the model’s performance on different subsets of the data, providing an estimate of its predictive ability and generalisation performance. The fertility index will be evaluated for its discriminatory ability in predicting chances of pregnancy based on the area under the receiver operating characteristic curve (AUROC), with value >0.80 indicating that the model exhibits a good discriminatory ability or predictive value.

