## Discussion

In this study, we will comprehensively investigate multiple factors in males, including clinical, biological, behavioural, lifestyle, environmental and molecular characteristics, to understand their relationships with male reproductive health and successful pregnancy. State-of-the-art automated technology integrated with artificial intelligence algorithms will be used to measure sperm DNA fragmentation and assess biofluid oxidative status. This approach will provide crucial insights for reproductive healthcare, defining male fertility status and guiding fertility treatment decisions. Additionally, the assessment of sperm gene expression and DNA methylation will allow understanding of how male exposures affect fertility at a molecular level, aiding in identifying novel candidate biomarkers for predicting the chances of conception and potentially offspring health. These advancements represent a significant step towards implementing an entirely new class of precision medicine in male fertility care, enabling personalised management plans.

Furthermore, the study aligns with the POHaD paradigm, which recognises optimal paternal health as an essential component, along with maternal health, to create a favourable environment that has tremendous potential to influence the birth and growth of healthy children. These efforts will help mitigate the burden of the transgenerational cycle of chronic disease development within families and the wider population. Importantly, the findings of this study will raise awareness among healthcare agencies and the general public about the significant role of men (an essential but often neglected component) and the importance of optimising men’s health during preconception to improve reproductive health outcomes. By focusing on the father’s role in reproductive health outcomes through an evidence-based approach, there is a move to address the disproportionate burden placed on women and promote equity in healthcare and society, in addition to the growing evidence of the influence of sperm quality on reproductive outcomes.

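### The planned AUROC cannot support the promised tertiary-care use of the fertility index, because every case is non-pregnant at entry, every control is already pregnant, and nobody is followed

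*Protocol article*

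**What the plan says.** All references are to the Protocol article.

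- **Promised use (Statistical analysis plan, Aim 2).** The index is to give an overall probability from summed points, with more points meaning a better chance of pregnancy. Further versions add male metabolic biomarkers and semen parameters, "catering to different levels of complexity for application in primary and tertiary care settings".
- **Performance (same section).** Ten-fold cross-validation on the study sample is offered as an estimate of predictive ability and generalisation. An AUROC above 0.80 is taken to indicate good discrimination or predictive value for the chance of pregnancy.
- **Recruitment (Participants and recruitment).** Of the cases it says: "Couples from the case group will be recruited from the infertility clinics in KKH". Controls come from antenatal clinics at the same hospital. The team will also "leverage the Healthy Early Life Moments in Singapore (HELMS) programme to recruit potential cases and controls".
- **Case eligibility (Inclusion criteria, Cases).** "Couples who are not able to conceive for at least 12 months of regular, unprotected intercourse".
- **Control eligibility (Inclusion criteria, Controls).** Fertility is shown by "female partners who are currently pregnant and with viable intrauterine pregnancy at gestational weeks of less than or equal to 16", after trying for no more than 12 months.
- **Follow-up (Data collection and management).** "During the study visit (the only single timepoint visit" is how the single contact is described. Neither Table 1 nor the analysis plan lists a later pregnancy or treatment outcome.

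**The concern.** In an infertility clinic the useful question about an index of this kind is which attending couples will go on to conceive. Answering it needs couples from that setting with both outcomes, some who later conceive and some who do not. Here the outcome is fixed at entry and follows the group a couple was recruited into. The model therefore learns what distinguishes couples who have not conceived after 12 months from couples who are already pregnant. That is a legitimate contrast, but a different one.

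At stake is what the study may conclude. If the cross-validated AUROC passes 0.80, the text of Aim 2 would let the authors present the extended index as a predictor of pregnancy for clinic use, although its performance there was never testable. Aims 1 and 3 are not affected.

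**Working it through.** **1. The plan's own figures.** The sample-size arithmetic reproduces, and nothing in this point turns on it.
- BMI difference 1.3, SD 4, two-sided 5%, 90% power: n per group = 2 × (1.960 + 1.282)² × 4² / 1.3² = 198.96, so 199 (plan: 200). Then 400 × 1.2 = 480.
- Events per variable: 150 / 0.48 = 312.5, so 313. Then 313 × 1.2 = 375.6, so 376.

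The plan gives no figure for performance within infertility-clinic couples.

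**2. Outcome by recruited group.**

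| Group | Source | Outcome at entry | Later outcome collected |
|---|---|---|---|
| Cases (240) | Infertility clinics; some possibly from HELMS | Non-pregnant after at least 12 months (all) | None |
| Controls (240) | Antenatal clinics; some possibly from HELMS | Pregnant, at most 16 weeks (all) | None |

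**3. What can be estimated.** AUROC is the probability that a randomly chosen couple with the outcome scores higher than a randomly chosen couple without it. It needs at least one couple of each kind.
- Pooled sample: 240 pregnant and 240 not, so it can be estimated. It compares recruited controls with recruited cases.
- Infertility-clinic cases alone: 0 pregnant, so it is undefined. Calibration for later pregnancy cannot be estimated either, because no later pregnancy is observed.

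Ten-fold cross-validation divides the same two groups and creates no outcome variation within the cases. It corrects for overfitting to this contrast and does not turn it into another contrast.

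**4. Illustration that the two quantities can diverge.** Assumptions, not from the documents: the score is normal with SD 1 in each group, the groups differ by d, and later pregnancy among clinic couples is unrelated to the score. Pooled AUROC = Φ(d/√2).
- d = 1.19: Φ(0.841) = 0.80
- d = 1.50: Φ(1.061) = 0.86

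A simulation of 2,000 studies of 240:240 gave mean pooled AUROCs of 0.80 and 0.86. AUROC for later pregnancy among the 240 cases averaged 0.50 in both settings, whether 20%, 30% or 40% of them later conceived. The value 0.50 follows from the no-relation assumption. The example shows only that meeting the 0.80 criterion does not rule it out.

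**5. Do other parts of the plan close the gap?**
- *HELMS* is named as a source other than the antenatal and infertility clinics, and its couples enter under the same eligibility rules, with outcome fixed.
- *The repeat analysis by assisted and unassisted conception* can classify only couples who conceived. No case contributes a conception.
- *The limitations in the Discussion* cover recall bias, residual confounding and geography, and not this point.

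**The case against.** The strongest reply is that this is one forward-looking clause in a development-stage article. The clause links the versions to levels of complexity, so tertiary care may simply mean a place where semen and biomarker tests are available. Controls come from antenatal clinics in the same hospital, and the article does not claim validated performance in infertility clinics. Part of this stands: tertiary care is not defined, and the point is best stated for infertility-clinic couples. It does not remove the problem. Already-pregnant couples are not users of an index that predicts pregnancy, and Aim 2 reads the AUROC as predictive value for the chance of pregnancy without saying whose.

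Three stronger readings are tempting, and the documents do not support them.

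- *Clinic couples would be given a probability that is too high.* A reader might infer this because Aim 2 weights to pregnancy within a year in the population, a window that the cases have already passed. The direction is not shown. Aim 2 lists duration of active conception attempts as a candidate predictor. Cases have at least 12 months and controls at most 12, so if duration is kept it nearly separates the groups and could push clinic probabilities too low. Nor can the 48% in the Sample size section serve as the benchmark: it is an input to the events-per-variable calculation, is given without a time window, and is not stated to be the weighting target. Even if it were used, an index scores couples on their covariates. With normal scores and 48% prevalence (both assumed), the mean predicted probability among cases at AUROC 0.80 is about 0.35, well below 48%.
- *The index is stated to be for treatment decisions.* The Discussion does speak of "defining male fertility status and guiding fertility treatment decisions", but that sentence follows one on automated measurement of sperm DNA fragmentation and oxidative status. It does not name the index, and the link is at most indirect, through the version with semen parameters.
- *The index would be sound if limited to couples starting to try.* The study enrols none: cases have tried for at least 12 months and controls are pregnant.

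**Conclusion.** The point holds in a limited form. As designed, the study provides no information on how well any version of the index discriminates or is calibrated for later pregnancy among infertility-clinic couples. The number of observed pregnancies among the cases is 0, so the gap is one of design and not of precision, and a larger sample would not close it. The AUROC and the 0.80 criterion describe separation of recruited cases from recruited pregnant controls.

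This rests on the stated eligibility rules, the stated single visit, and the absence of any later outcome from Table 1 and the analysis plan. It needs no modelling assumption; the 0.50 figure is an illustration only. The true within-clinic performance may be good or poor. The documents do not show that the index is wrong for these couples, or in which direction it would err. A change of wording should be made, since it alters what the study may conclude.

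**What to change.** In Aim 2 of the Statistical analysis plan:

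1. Remove the tertiary-care application, or make it conditional on external validation in infertility-clinic couples who are followed for pregnancy.
2. Beside the AUROC and the 0.80 criterion, state that they describe separation of the recruited cases from the recruited controls, and not prediction of future pregnancy among couples who have already tried for 12 months.

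Optionally, with participants' consent, ascertain later pregnancy in the cases and report discrimination and calibration among the cases alone. Assisted conceptions and pregnancies managed elsewhere would limit this and should be acknowledged.

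Items 1 and 2 cost only wording and a narrower claim; recruitment, measurements and sample size stay as they are. The optional step adds consent wording and outcome ascertainment.

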### Statistical analysis plan

#### Aim 1

We will use multivariable logistic regression model to assess the association between case versus control status and male factors, adjusting for potential confounders such as male sociodemographics, general health, as well as female factors which are correlated with both male factors and successful pregnancy. We will identify these potential confounders through a literature review and conceptual framework, guided by directed acyclic graphs. We will explore propensity score methods, such as inverse probability weighting, to ensure balanced distribution of confounders across case and control groups. We will use the least absolute shrinkage and selection operator regression to select male factors for inclusion in the final model.

#### Aim 2

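### As written, 10-fold cross-validation follows outcome-driven predictor selection, so the AUROC judged against 0.80 is optimistic

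*Protocol article*

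**What the plan says.** The statistical analysis plan section of the protocol article sets out the following order.

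- **Aim 1:** "We will use the least absolute shrinkage and selection operator regression to select male factors for inclusion in the final model".
- **Aim 2, entry:** "We will include the identified male factors from aim 1, along with female factors which are known to be associated with successful pregnancy". Clinical and other maternal variables are then added "in the logistic regression to further select the predictors".
- **Aim 2, model choice:** "The best-fitting model will be determined using Akaike’s information criteria". Integer points are derived from the coefficients of the resulting model.
- **Aim 2, extended versions:** the procedure is repeated "by including male metabolic biomarkers and semen parameters that are associated with successful pregnancy in the weighted logistic regression".
- **Aim 2, validation:** "Subsequently, we will use 10-fold cross-validation to assess the performance of the derived logistic regression models and respective fertility index scores". The article describes this as "providing an estimate of its predictive ability and generalisation performance" and takes an AUROC above 0.80 as good discrimination.

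Continuous variables are handled separately: "all continuous variables will be categorised based on clinical thresholds or appropriate percentiles prior to the analysis".

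The article describes no hold-out sample, optimism correction or external validation, and does not say that any selection step is repeated within the folds.

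**The concern.** Cross-validation estimates performance in new couples only if the held-out couples played no part in building the model. Here four steps use case or control status: LASSO, the further predictor selection, AIC, and the entry of biomarkers because of their association with pregnancy. If these run once and only the coefficients are re-estimated in each fold, every held-out couple has already influenced which predictors are present. Noise predictors that happened to separate cases from controls in this sample will also tend to separate them in its held-out tenth.

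The AUROC threshold is the only numerical performance criterion stated for the index, which is the main product of Aim 2 and is meant for community, primary and tertiary care. An optimistic estimate could label the index good when it is not. It would also distort comparisons between index versions, because versions screened from more candidates tend to gain more.

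**Working it through.** **Figures in the plan.** The 0.80 threshold has no derivation to reproduce. The sample size fixes the n for the check, and it reproduces.

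- BMI route (difference 1.3, SD 4, two-sided 5%, power 90%): n per group = 2 × (1.960 + 1.282)² × 4² / 1.3² ≈ 199. The total is 398 against the stated 400, and 398 × 1.2 = 477.6 against 480.
- Events-per-variable route: 15 × 10 / 0.48 = 312.5, rounded to 313, and 313 × 1.2 = 375.6 against 376.

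These figures do not bear on whether the bias exists.

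**Inputs that the article does not give (assumptions).** These are the number of candidate male factors and their effects. Table 1 of the article has about 38 male headings before molecular data: 21 sociodemographic, clinical and lifestyle, 4 anthropometric and blood pressure, 8 biochemical and 5 semen. Some would serve as confounders, and others contain several variables. A range of 30 to 100 candidates was therefore used, and a smaller set was checked separately.

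**Main simulation.** Each of 60 runs per scenario had 240 cases and 240 controls. Where signal was present, there were 6 real male factors and 4 real female factors among 9 female or clinical candidates, with log-odds 0.3 or 0.5 per SD. Variables were split at the median. LASSO (penalty by 5-fold cross-validation) selected male factors, and backward AIC then worked on those plus the 9 others. Three AUROCs were compared:

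- A: 10-fold cross-validation refitting only the coefficients of the already selected model;
- B: 10-fold cross-validation repeating LASSO and AIC in each training fold;
- C: the selected model applied to 8000 new couples, taken as the truth.

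| Log-odds | Male candidates | A | B | C | A − C | Runs with A > 0.80 | Runs with C > 0.80 |
|---|---|---|---|---|---|---|---|
| 0 | 30 | 0.559 | 0.499 | 0.500 | 0.059 | 0% | 0% |
| 0 | 60 | 0.576 | 0.505 | 0.500 | 0.076 | 0% | 0% |
| 0.3 | 30 | 0.707 | 0.663 | 0.671 | 0.036 | 0% | 0% |
| 0.3 | 60 | 0.723 | 0.658 | 0.662 | 0.060 | 0% | 0% |
| 0.5 | 30 | 0.778 | 0.748 | 0.759 | 0.019 | 13% | 0% |
| 0.5 | 60 | 0.788 | 0.741 | 0.749 | 0.038 | 27% | 0% |
| 0.5 | 100 | 0.798 | 0.737 | 0.745 | 0.052 | 47% | 0% |

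Differences were taken before rounding; their simulation standard errors are 0.003 to 0.006. The gap A − C grows with the number of candidates at each effect size. B lies within about 0.01 of C throughout, so selection inside the folds removes the bias.

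**Smaller candidate sets.** A second simulation used 15 to 20 male candidates, backward AIC without LASSO, the same 6 and 4 real factors, 9 female candidates and 60 runs per scenario. With log-odds 0.3 to 0.5, cross-validation after selection exceeded the truth by 0.006 to 0.026. At 0.5 both exceeded 0.80 in every run, and at 0.3 almost neither did. At 0.4 with 20 candidates, 68% of runs passed on the cross-validated AUROC and 25% on the true one. Wrong passes concentrated where the true AUROC was about 0.79 to 0.80. The two designs differ, so their gaps can be compared but their AUROC levels cannot.

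**Cut-points.** Recomputing percentile cut-points in each training fold changed B by at most 0.003.

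**Precision at the threshold.** The Hanley-McNeil standard error at AUROC 0.80 with 240 and 240 is 0.020, so a 95% interval is about 0.80 ± 1.96 × 0.020, or 0.76 to 0.84.

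**The case against.** **The article does not state that selection runs once on all 480 couples.** This is true. It is a condensed account, fold-level mechanics may sit in a fuller plan, and nothing expressly excludes repeating selection within folds. What stands is that the conclusion concerns the order as written. The validation comes afterwards and is applied to models already derived, which makes selection before cross-validation the natural reading. Because the article also claims that the result shows generalisation performance, this is a stated procedure without its stated property, not merely an omitted detail.

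**The bias may be small for the main index.** Its male factors are to be easily accessible measurements, six female factors come from an earlier study, and 15 coefficients are expected. This stands in part. The 15 are retained coefficients and do not count the candidates screened, but a small candidate set would put the optimism near the lower end of the range. The female-only index should carry little, since its factors come largely from that earlier study; this is reasoned and was not simulated.

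**The 0.80 threshold is only a descriptive label.** No treatment or deployment decision hangs on it, and recruitment and data collection are unaffected. This stands and limits the severity.

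**Cut-points.** A reader might infer that they add to the bias. The article does not support this: they are clinical thresholds or percentiles set before the analysis, with no reference to the outcome, and their simulated effect was negligible.

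**Aim 1.** A reader might also infer that the list of male factors will be too long. That is a separate question. It depends on the LASSO tuning rule, which the article does not give, and does not follow from the order of cross-validation.

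**Conclusion.** Wrong as written; it should be fixed before analysis. Outcome-driven selection precedes cross-validation of the derived models and scores, so the AUROC set against 0.80 is optimistic and does not estimate generalisation performance.

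At 240 and 240 the optimism is about 0.01 to 0.08. The largest values in the main simulation came with no true signal, where the AUROC (0.576) is far from 0.80. With signal it was about 0.02 to 0.06 for 30 to 100 candidates, and 0.006 to 0.026 for 15 to 20. It tends to be larger for versions with more screened candidates, which makes the biomarker and semen versions the more exposed.

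A reader might infer that the index would often pass 0.80 while performing far worse. A simulated scenario with 100 independent candidates, 10 of them real (odds ratio about 1.5 per SD), does give 0.80 against 0.72, but the article nowhere gives 100 candidates. The supportable statement is that false passes occur mainly when the true AUROC lies somewhat below 0.80.

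All these sizes rest on assumed candidate numbers and effects. Integer rounding of points, prevalence weighting and multiple imputation were not modelled in the main simulation. The direction of the bias depends only on the order of steps being followed as written.

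**What to change.** State in the plan that the following are repeated within each of the 10 training folds, preferably with repeated cross-validation:

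- LASSO, including the choice of its penalty;
- the further predictor selection and the AIC step;
- the association-based entry of biomarkers and semen parameters in the extended versions;
- the assignment of points.

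Alternatively, use a bootstrap optimism correction that reruns the whole pipeline in each resample. Apply the 0.80 criterion to the resulting AUROC, reported with its 95% CI, and treat every index version in the same way so that comparisons are fair. If selection within folds is already intended, one sentence saying so settles the point.

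The cost is programming time and a lower reported AUROC. No new data are needed.

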### Objectives

The overall objective of this study is to determine the contribution of male factors to successful pregnancy after accounting for female factors and gain a deeper understanding of the biological mechanisms that underlie this relationship. Specifically, we aim to:

Identify male factors associated with the likelihood of pregnancy, independent of female factors.Develop a fertility index that integrates modifiable factors for both males and females to estimate the likelihood of pregnancy.Explore the relationships between male modifiable factors, oxidative status, sperm physical and molecular characteristics.

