Given that the fertility index comprises male and female factors, we will perform additional analyses to evaluate the individual performance of the index that includes only male factors or female factors using the AUROC. We will also evaluate the performance of the male factor index, with adjustment of female factor index.

#### Aim 3

We will use multivariable linear regression to examine the association between modifiable factors and semen parameters, adjusting for sociodemographic factors.

To understand the relationships between male factors and fertility indices across different conception methods, we will replicate the above analyses by examining outcomes based on assisted and unassisted conception. To assess potential selection bias in both studies, we will compare baseline characteristics between participants with and without a complete set of data. We will use multiple imputation by chained equation to handle missing values.^54^ Sensitivity analyses will be conducted using only samples with complete data. To further ensure robustness, we will test interactions between male and female factors and stratify analyses by key confounders. Statistical analyses will be conducted using the Stata Statistical Software.

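### The fertility index is meant to output a probability of pregnancy, but its only stated criterion, AUROC above 0.80, measures ranking and cannot show that the probabilities are right

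*Protocol article*

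**What the plan says.** All references are to the Protocol article.

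- Objectives, second aim: "Develop a fertility index that integrates modifiable factors for both males and females to estimate the likelihood of pregnancy".
- Statistical analysis plan, Aim 2: integer points are assigned to each factor, "allowing the estimation of overall probability by summing the points".
- The regression is weighted, "adjusting the model based on the updated prevalence of successful pregnancies within a year in the population to correct for sampling biases". The prevalence value is not given there.
- Model choice: "The best-fitting model will be determined using Akaike’s information criteria".
- Validation: "we will use 10-fold cross-validation to assess the performance of the derived logistic regression models and respective fertility index scores".
- Performance measure: "The fertility index will be evaluated for its discriminatory ability in predicting chances of pregnancy based on the area under the receiver operating characteristic curve", "with value >0.80 indicating that the model exhibits a good discriminatory ability or predictive value".
- The same measure returns for the partial indices, where the plan is to "evaluate the individual performance of the index that includes only male factors or female factors using the AUROC".

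The article names no measure of agreement between predicted and observed probabilities, such as a calibration slope, calibration curve or Brier score.

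**The concern.** The index has two jobs: to order couples by their chance of pregnancy, and to tell a couple what that chance is. AUROC addresses only the first. The article nevertheless fixes a threshold for it and treats passing as a sign of predictive value for a tool whose output is a probability.

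Several planned steps can distort the probabilities: 1:1 case-control sampling corrected by an external prevalence, data-driven selection of predictors, categorisation of continuous variables, and rounding of coefficients to integers. The index is intended for primary and tertiary care. If only the stated criterion were applied, an index whose high predictions are too high and low predictions too low could be credited with predictive value.

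**Working it through.** **1. The plan's own figures.** Under Sample size, 15 coefficients at 10 events each need 150 events. 150 / 0.48 = 312.5, rounded to 313, and 313 × 1.2 = 375.6, rounded to 376. The recruitment target is 400 × 1.2 = 480 couples, 240 per group. These figures reproduce and are not in dispute. The 15 coefficients are described as male factors. Aim 2 adds female age, BMI, smoking exposure, diet, alcohol and folic acid (6), and attempt duration, sexual health issues and probable depression (3). At one coefficient each, 15 + 9 = 24. I use 25 as an assumption, with 35 as an upper illustration because categorised variables can need more than one coefficient.

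**2. AUROC does not respond to monotone distortion.** Take a normally distributed predictor with AUROC set to 0.82 (assumption) and prevalence 0.48. The correct probabilities have a Brier score of 0.173. Doubling all centred log-odds gives a calibration slope of 0.5 and a Brier score of 0.185. AUROC is 0.82 in both. This illustrates the principle only. Real overfitting also disturbs the ranking, so it needs step 4.

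**3. Expected slope by formula.** Expected slope ≈ 1 − p / LR, with LR = −n ln(1 − R²). Inputs: n = 480, and Cox-Snell R² = 0.261, the value for AUROC 0.80 at a 50% event fraction. LR = −480 × ln(0.739) = 145.2.

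- p = 15: 1 − 15/145.2 = 0.90
- p = 25: 1 − 25/145.2 = 0.83
- p = 35: 1 − 35/145.2 = 0.76

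**4. Simulation with 10-fold cross-validation.** 240 cases and 240 controls, true AUROC 0.80, independent predictors of equal strength, ordinary logistic regression.

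| Coefficients | Mean cross-validated AUROC | Runs above 0.80 | Mean slope in runs above 0.80 |
|---|---|---|---|
| 15 | about 0.78 | 24% | about 0.85 |
| 25 | about 0.775 | 11% | about 0.77 |
| 35 | about 0.76 | 6% | about 0.70 |

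The pass rates come from 200 runs per setting. The simulated slopes lie below those in step 3, which is a large-sample approximation using the full 480. Both are below 1.

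**5. What such slopes mean.** With no intercept error, a predicted 90% has log-odds ln(9) = 2.197.

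- Slope 0.85: 0.85 × 2.197 = 1.867, or 86.6%.
- Slope 0.77: 0.77 × 2.197 = 1.692, or 84.4%.

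By symmetry, a predicted 10% corresponds to about 13.4% and 15.6%.

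**6. Precision of the criterion.** The Hanley–McNeil variance at A = 0.80 with 240 per group uses a = A/(2 − A) = 0.6667 and b = 2A²/(1 + A) = 0.7111. The variance is [0.16 + 239(0.6667 − 0.64) + 239(0.7111 − 0.64)] / 240², so SE = 0.020. The 95% interval is 0.80 ± 1.96 × 0.020, about 0.76 to 0.84.

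**The case against.** The best defence is that this is mainly missing detail in a condensed article. The sentence says the index is evaluated for discrimination, which is what AUROC measures. The article does not call AUROC the only measure or 0.80 a formal success rule, and an analysis plan that is not shown may include calibration. That stands, so it would go too far to infer that calibration will not be examined. What remains is wording the article itself fixes: the threshold is also read as predictive value, and an unseen calibration plot would not make that reading correct.

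Two stronger readings are tempting and are not supported.

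- **That the threshold is blind to overfitting.** It is not. Overfitting disturbs ranks, and the mean cross-validated AUROC falls below 0.80 in every row of the table, so most overfitted models in that setting would fail. The point concerns those that pass.
- **That the probabilities will be far too low overall.** A reader might pair the 48% pregnancy rate under Sample size with the complement of the one-in-six figure in the Introduction, about 83%, and conclude that the average prediction will be badly wrong. The article does not say that 48% is the weighting prevalence, nor does it state 83% as the true rate. Calibration inside the study could not reveal such an error anyway: in a simulation weighted to 48%, the weighted mean prediction was 48.2% against 48.0% observed, whatever the true population rate.

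The prevalence weighting is a genuine attempt to set the overall level, and AIC is likelihood-based. Neither checks the slope of the final score or the effect of rounding to integers.

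**Conclusion.** The concern holds in a limited form. AUROC above 0.80 supports a statement about discrimination. It does not support predictive value for an index that reports probabilities, and the article states no other criterion. Among simulated models that pass the threshold, predictions are too extreme by a moderate amount: mean slope about 0.85 with 15 coefficients and about 0.77 with 25, or roughly 3 to 6 percentage points at a predicted 90%.

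These sizes assume a true AUROC of 0.80, independent predictors of equal strength, and no weighting, variable selection, categorisation or rounding in the simulation. The count of 25 is also an assumption. This should be corrected before the index is developed. It does not invalidate the design.

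**What to change.** 1. Confine the 0.80 statement to discrimination, drop the reference to predictive value, and report AUROC with its 95% confidence interval.
2. In the planned 10-fold cross-validation, repeat variable selection, categorisation and point assignment within each fold. Report the weighted calibration slope and calibration curve for each model and each integer score.
3. Claim that the index estimates a probability only if those results are acceptable. Shrinking coefficients by the cross-validated slope before assigning points is an option, not a requirement.
4. State that the overall level of the probabilities depends on the external prevalence used for weighting, that internal calibration cannot verify it, and show results over a range of prevalences.

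The cost is a little more analysis code and some rewording, with no extra participants or data. The score may look less favourable.
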